## Consolidated Framework for Implementation Research

The ASAP Research team will directly apply implementation science constructs to the qualitative data. Using methods developed by [name] for RE-INSPIRE to rate and score for construct and valence (i.e., positive, neutral or negative) across the domains of Process (Planning, Reflecting and Evaluating, and Champions), Inner Setting (Goals and Feedback, Networks and Communications, and Access to Knowledge & Information), Outer Setting (External Policy and Incentives), and Interventional Characteristics (Evidence Strength & Quality).

## Notes from Interactions the ASAP Research Team has with Champions and Others Involved in Local Implementation of QI ASAP Initiatives

**External Facilitation** interactions between ASAP Research personnel and local site personnel performing ASAP QI will include on average a monthly scheduled meeting as well as *ad hoc* interactions that occurs at the request of either local teams or ASAP Research personnel. Number of minutes by participant by type of contact will be recorded in an external facilitation tracker and notes from these interactions will be recorded in on a standardized external facilitation interaction template

**Monthly Collaborative Calls** will produce a combination of data which includes triumphs and barriers, lessons learned from the prior month, and short- and longer-term implementation goals reported by sites, notes taken by ASAP Research personnel, and an ASAP Research-personnel debrief that is recorded and transcribed after ASAP Collaborative calls

#### **Chart review from ASAP patients and patients at control sites**

Charts will be reviewed by ASAP Field Staff using local CPRS and centrally using Compensation and Pension Records Interchange (CAPRI) access to the electronic health records, by trained staff at the Indianapolis site using methods successfully employed in other quality assessment projects.

#### **Administrative Data**

Sources will include Corporate Data Warehouse [CDW] data, VA vital status files, VHA Support Service Center [VSSC], Decision Support System [DSS] Pharmacy Data, and the National Prosthetics Patient Database). These will include ICD codes for

### **5.7 Data Analysis**

**5.7.a. Data Analysis Overview** A stepped-wedge trial will be used, rather than an individual patient-level randomized trial, because the intervention program is implemented at the site-level. Although this trial could have been set-up as a parallel cluster randomized trial (CRT), we sought to examine the treatment effect of the ASAP program using fewer sites (given the resource constraints of the IIR program). Additionally, we chose the stepped-wedge design, as opposed to a before and after within each cluster design, because the latter approach may be biased, (e.g., if underlying rates of OSA diagnosis change during the study period). With a stepped-wedge we can account for the time-related trends by incorporating time as a covariate. Time may be included in the analysis as a categorical variable (i.e., allowing a time effect at each step), or using time as continuous variable (assuming a linear increase or decrease over time).

**5.7.b. Period Classification** The stepped-wedge design allows for 8 mutually exclusive, 7-month data periods. Effectiveness outcome data for each site for each data period will be classified as either control or intervention. The active implementation period will be considered as the intervention phase. If a patient has more than one stroke/TIA, then only the first will be included in the analysis (i.e., patients in each time increment are unique). If a patient has more than one stroke/TIA event, but one occurs in the baseline period and one during the active implementation period, then the event during the active implementation period will be used. The stepped-wedge design allows site-level estimates of

proportions on 8 different cross-sectional samples. Thus, we will have repeated information on each site.

**5.7.c. Specific Aim 1 (Effectiveness) Analyses** Program effectiveness will be evaluated by a single, primary outcome (diagnostic rate). The diagnostic rate is defined as PSG completion within 30 days of presentation for the index stroke or TIA. **Effectiveness Outcome Ascertainment** We will seek to iteratively improve the CDW algorithms by comparing data to that of the chart review data (e.g., NIHSS data). COVID-19 data has been added to our ASAP administrative data set. COVID-19 data will consist of a combination of: (1) patients with polymerase chain reaction or antigen test results positive for severe acute respiratory syndrome coronavirus 2 (SARS-CoV-2) and; (2) from the VA National Surveillance Tool (NST). Also, pertinent dates related to the impact of the Philips Respironics Recall, indicating VHA-wide availability of PAP, have been added to our data.

Admissions for ischemic stroke and TIA to VAMCs have shown a decline during the COVID-19 pandemic. Furthermore, patients admitted to a VAMC with COVID-19 are not candidates to receive positive airway pressure (PAP) during the index hospitalization.

In considering analyses of the primary outcome, a sensitivity analysis will include re-running the final model with the inclusion of a facility-level, time-varying measure of COVID-19 burden. Although, inclusion of control sites which allows us to adjust for secular time trends may be sufficient to account for the effect of COVID-19 in the model.

We would also merge these COVID-19 data with data from an operational/quality improvement survey we conducted with [name] to understand how COVID-19 affected the services provided by the Sleep Program across VHA, as well as to understand how VAMC sleep programs might move forward once a reopening occurs. Analyses using the COVID data would include whether a higher burden of COVID-19 within a responding facility was associated with higher rates of self-reported interruption of sleep services offered within a facility. We will obtain Medicare data for all stroke/TIA patients during the active implementation period; however, given delays in Medicare data availability, we will only plan to include these data in the primary analysis if they are available for all 3 time periods. We anticipate having no more than 1 million subjects within our administrative data sets. This number has been approximated with the inclusion of the COVID population, which at this time, continues to grow. Secondary to the large scale of the COVID population, we have been generous in our estimation of those included in the administrative cohort.

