## 2. Objectives

Utilizing a Hybrid Type I, randomized, stepped-wedge trial at 6 diverse VAMCs as intervention sites and 30 usual care control sites, to implement and evaluate the effectiveness and sustainability of implementation strategies utilized in an Addressing Sleep Apnea Post-stroke (ASAP) program designed to improve facility-level diagnosis and management of OSA. These objectives will be accomplished through the following specific aims:

**Specific Aim 1:** Evaluate the effectiveness of an intervention for the early diagnosis and treatment of OSA among Veterans with ischemic stroke and TIA. The intervention program will include a systems redesign Virtual Collaborative and data monitoring. ASAP includes external facilitation and audit and feedback as implementation strategies, which will be assessed during the intervention period. Sites will locally-tailor and implement an Addressing Sleep Apnea Post-stroke (ASAP) quality improvement program. The sites will choose a diagnostic strategy (i.e., unattended polysomnography [PSG]/home sleep test [HST], in-laboratory PSG, direct to auto-titrating [auto]-PAP) and a therapeutic strategy (e.g., in-laboratory PAP titration, auto-PAP). The primary effectiveness outcome, evaluated at the facility-level, will be the 30-day sleep apnea diagnostic rate. The three secondary effectiveness outcomes will be 1. the 30-day

treatment rate, 2. the 90-day recurrent vascular event rate and 3. the 90-day all-cause readmission rate. We hypothesize that the: mean facility diagnostic rate (PSG within 30 days of presentation) will be 70% for eligible patients during intervention periods vs 7% for controls; the mean facility treatment rate (PAP initiation within 30 days of presentation) will be 50% for intervention vs 2% for controls; mean facility 90-day recurrent vascular event rate (stroke, MI/acute coronary syndrome [ACS], congestive heart failure [CHF] and all-cause mortality) will be 3.5% for intervention vs 10% for controls; and; mean facility 90-day all-cause readmission rate will be 20% for intervention vs 33% for controls. Chart review and administrative data will be used to ascertain outcomes.

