In considering the types of Veterans who would be eligible for sleep apnea diagnostic testing or treatment, we should first note that at all times treating providers (the target of the research) will hold patient safety in the highest regard. Thus, by keeping contraindications to PAP therapy in mind, providers may decide to exclude patients from PAP therapy. This would be the case for Veterans who meet inclusion criteria for the study (i.e., being admitted to an ASAP VAMC with the diagnosis of ischemic stroke or TIA who do not have an existing diagnosis of sleep apnea) but their healthcare provider, in the course of delivering routine clinical care, makes the decision that a given Veteran has a contraindication to PAP therapy. Inclusion criteria would include patients admitted to an ASAP VAMC with the diagnosis of an ischemic stroke/TIA without a prior diagnosis of OSA. Exclusion criteria for Veterans will include being admitted to an ASAP VAMC with a diagnosis other than ischemic stroke or TIA (e.g., syncope, seizure), Veterans not admitted to a VAMC for their acute cerebrovascular care

(e.g., presented to the Emergency Department and transferred to a non-VAMC), or a known history of sleep apnea.

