## **Analysis of the Primary Effectiveness Outcome**

### **Diagnostic Rate Analysis**

A generalized linear mixed model will be fit to the patient-level outcome of diagnostic testing (yes/no) to conduct facility-level inference. The primary effect of interest is the effect of the intervention during active implementation versus baseline. Control sites are included to add accuracy in estimation of the secular time trend. A non-exact match approach is planned for this analysis (i.e., unconditional) since this model is being fit to patient-level data which will be used to conduct facility-level inference and there is no guarantee that patients in control sites that were loosely matched to an intervention site using facility factors are similar. This approach will use all available control site data without pairing specific control sites to each ASAP site. Effects in the model include a site-level indicator of intervention site vs control site, indicator for each site and data period corresponding to active implementation or sustainability phase, and time (as categorical, indicating each 7-month data period). The model will also include a random intercept for site to account for potential correlation among patients from the same site. Our interest is in testing the effect of the ASAP intervention on the proportion of patients who are diagnosed at the site-level. This model will also be fit adjusting for any important patient covariates (i.e., stroke severity). Both unadjusted and adjusted results will be reported. Contrasts from the model will also be estimated. All statistical tests will be two-sided, with p-values < 0.05 considered statistically significant. All analyses will include checking of assumptions and model fit.

**Analysis of Secondary Outcomes** As described above, because the treatment rate can only be assessed among the patients who have been diagnosed, we will be limited in our analysis of treatment. If several patients are diagnosed in the during the control phase (which is unlikely), we would use the same mixed model approach as with other outcomes. However, because we expect to have very

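### A later stroke/TIA in active implementation displaces a patient's baseline event, so baseline membership at ASAP sites depends on the future, while control sites on the natural reading are unaffected

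*Protocol*

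**What the plan says.** Protocol section 5.7.b (Period Classification) begins with a simple rule: "If a patient has more than one stroke/TIA, then only the first will be included in the analysis". It then reverses the rule for a patient with one event in baseline and one in active implementation: "then the event during the active implementation period will be used". No reason is given. The stated aim, that patients be unique within each time increment, is already met by the first-event rule.

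Three other provisions matter:

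- **Eligibility (section 5.4).** Veterans are excluded for a diagnosis other than ischemic stroke or TIA, for not being admitted to a VAMC, "or a known history of sleep apnea". The footnote to Table 2 (section 5.1.b) also removes patients with a PSG in the prior 5 years from the potentially eligible count. Section 5.4 does not repeat that exclusion.
- **Primary contrast (Diagnostic Rate Analysis).** "The primary effect of interest is the effect of the intervention during active implementation versus baseline". The outcome is PSG completion within 30 days of presentation (section 5.7.c).
- **Control sites.** Section 2 plans "6 diverse VAMCs as intervention sites and 30 usual care control sites". In the model, "Control sites are included to add accuracy in estimation of the secular time trend", and their data are used "without pairing specific control sites to each ASAP site".

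**The concern.** Whether a baseline patient is analysed as a baseline patient is decided by something that happens later. That is selection on the future, and it touches two outcomes.

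For the primary outcome, a patient found to have sleep apnea after the baseline event is no longer eligible at a second event and cannot be moved. Those moved are therefore mainly patients not diagnosed after the baseline event, and their removal raises the baseline diagnostic rate.

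For the 90-day recurrent vascular event rate, stroke and TIA are components of the outcome. A recurrence that falls after kick-off can become the patient's active-phase index event, and both the patient and the event then leave baseline.

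Control sites have no active phase to trigger the exception and, being unpaired, no notional start date. In the same calendar period, ASAP active samples keep patients who had an earlier in-study event, while control samples under the first-event rule drop them. The categorical period effects shared by the two groups of sites then rest on differently selected patients. None of the analyses listed under Specific Aim 1 Sensitivity Analyses addresses this.

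**Working it through.** **Inputs from the protocol.** Control-phase diagnostic rate 7%; about 64 patients per site per 7-month period (111 × 7/12 = 64.75); active phase 3 × 7 = 21 months; power target 7% vs 15%; hypothesised rates 70% vs 7% for diagnosis and 3.5% vs 10% for 90-day events; OSA prevalence 70-80%.

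**Assumption.** The protocol gives no repeat stroke/TIA rate. Let f be the share of baseline patients moved, taken as 5%, 10% and 15%. Per site-period that is 64 × f = 3.2, 6.4 and 9.6 patients at ASAP sites, and none at control sites on the natural reading.

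**Primary outcome, upper bound.** If every moved patient was untested after the baseline event, the baseline rate becomes 0.07/(1 − f):

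- f = 0.05: 0.07/0.95 = 7.4%
- f = 0.10: 0.07/0.90 = 7.8%
- f = 0.15: 0.07/0.85 = 8.2%

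**Allowing PSG-negative patients to move.** These patients count as successes on the primary outcome but have no sleep apnea history. Take 30% of tested patients as negative, the upper end implied by 70-80% prevalence, and let m be the chance of moving for anyone not excluded. The baseline rate is 0.07(1 − 0.3m) / [0.07(1 − 0.3m) + 0.93(1 − m)]:

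- m = 0.05: 0.06895/(0.06895 + 0.8835) = 7.2%, against 0.07/(0.07 + 0.8835) = 7.3% if no tested patient can move
- m = 0.15: 0.06685/(0.06685 + 0.7905) = 7.8%, against 0.07/(0.07 + 0.7905) = 8.1%

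The correction is small.

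**Effect on the contrast.** Holding the active rate fixed, the largest shift (8.2%) reduces 70 − 7 = 63 points to 61.8, and 15 − 7 = 8 points to 6.8. A 6.8-point difference lies between the 13.5% row (6.5 points) and the 14% row (7 points) of Table 3. Linear interpolation, (6.8 − 6.5)/0.5 = 0.6 of the way, gives power of 0.84 + 0.6 × 0.05 = 0.87 at CV 0.3 and 0.79 + 0.6 × 0.06 = 0.83 at CV 0.8. Table 3 gives 0.95 and 0.93 for 15%. This is rough, because the variance also changes a little.

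**90-day event rate, upward mechanism.** If every moved patient was event-free at 90 days, the baseline rate is 0.10/(1 − f) = 10.5%, 11.1% and 11.8%. This is an upper bound.

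**90-day event rate, downward mechanism.** Consider the last baseline period, with presentations uniform over 7 months, and assume a share s of the 10% composite is a stroke/TIA that qualifies as a new index event. A patient presenting u < 3 months before kick-off loses a counted event with probability 0.10 × s × (3 − u)/3. Averaged over 7 months this is 0.10 × s × 1.5/7.

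- s = 0.2: loss 0.0043; rate (0.10 − 0.0043)/(1 − 0.0043) = 9.6%
- s = 0.6: loss 0.0129; rate (0.10 − 0.0129)/(1 − 0.0129) = 8.8%

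**Both mechanisms together.** With an assumed 6% per year recurrence, about 8.8% of that period's patients are event-free at 90 days and recur later in the active window. Removing them as well:

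- s = 0.2: 0.0957/(0.9957 − 0.088) = 10.5%
- s = 0.6: 0.0871/(0.9871 − 0.088) = 9.7%

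The net shift crosses 10%, so its sign is not determined.

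**The case against.** The strongest reply is that the rule is written down, reproducible and affects a minority of patients. On the primary outcome it raises the baseline rate, so it works against the intervention and is minor beside an expected 70%. That is correct, and it limits the severity. It does not extend to the 90-day event rate, where the sign is open.

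Some stronger readings are tempting, but the protocol does not support them:

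- **That baseline loses only diagnostic failures.** The outcome is PSG completion, and section 5.4 excludes known sleep apnea, not prior testing. A patient tested negative after the baseline event could still be moved unless the prior-PSG exclusion in the Table 2 footnote also governs the analysis cohort.
- **That the 90-day baseline rate is inflated to 10.5-11.8%.** That requires every moved patient to be event-free at 90 days. It also ignores the lost recurrences, which affect only patients discharged within 90 days before kick-off and only the stroke/TIA part of the composite.
- **That a total number of moved patients per site can be stated.** The number of baseline periods per wave is in Figure 1, which is not shown. Eight periods (section 5.7.b) and a 3.5-year span, which holds 42/7 = 6 periods (section 5.1.a), imply different layouts.

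It can also be said that the protocol is silent on repeat events at control sites. That is true: that nobody is moved there is an inference. It is a firm one, because the exception is triggered by an active implementation period that those sites do not have.

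**Conclusion.** The concern holds as a should-fix. Section 5.7.b makes baseline membership at ASAP sites depend on a later event, and control sites as used in the model cannot correct for it.

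Under the assumed 5-15% moved, the baseline diagnostic rate rises from 7% to at most about 7.4-8.2%. With the active rate unchanged, this is a small bias toward the null. It is trivial against 70% but visible against the 15% used for power. A reader might infer that the rule could manufacture a positive primary result; this calculation points the other way.

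For the 90-day recurrent vascular event rate the direction is not fixed. In the illustration the last baseline period ends between 9.7% and 10.5% with both mechanisms, and the upward mechanism alone is bounded by about 10.5-11.8%. The bias on that outcome therefore cannot be called conservative.

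All sizes rest on assumed recurrence rates and, for the event rate, on an assumed stroke/TIA share. The structural point does not.

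**What to change.** Delete the exception in section 5.7.b. Use each patient's first eligible stroke/TIA in the whole study window, at every ASAP and control site, classified by the phase at presentation. State explicitly that the same rule applies at control sites. Any depletion of patients with earlier events then arises by the same rule at both kinds of site, and the shared period effects can reflect it. The protocol should also say whether the prior-PSG exclusion in the Table 2 footnote applies to the analysis cohort.

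If repeat events are wanted, add a sensitivity analysis with one event per patient per 7-month period at every site, allowing for within-patient correlation.

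The cost is one sentence of protocol text and a small change to cohort construction. No new data are needed. Under the assumption above, about 3 to 10 patients per ASAP baseline site-period are counted in baseline instead of active implementation.

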## Addressing Sleep Apnea Post-stroke (ASAP) multisite research project

### 1. Introduction

Approximately 11,000 Veterans present to a VAMC annually with an acute ischemic stroke or TIA. The cornerstone of secondary stroke/TIA prevention includes delivering timely, guideline-concordant vascular risk factor management. Over the past decade, OSA has been recognized as a potent, underdiagnosed, and inadequately treated cerebrovascular risk factor. OSA is very common among patients with stroke/TIA with a prevalence of 70-80%. Despite being highly prevalent, 70-80% of patients with OSA are neither diagnosed nor treated. History, physical examination, and screening instruments (e.g., Berlin Questionnaire) are inaccurate among patients with cerebrovascular disease. Given that no combination of symptoms or physical examination findings has adequate sensitivity or specificity for the diagnosis of OSA post-stroke/TIA, only PSG or auto-PAP (used diagnostically) can identify disease status post-cerebrovascular event. Recognizing these concerns, the AHA/ASA guidelines recommend that a sleep study (as opposed to screening questionnaires) should be used to identify the presence or absence of OSA among eligible patients with acute ischemic stroke or TIA.

The American Academy of Sleep Medicine (AASM) recommends PSG either conducted in a sleep laboratory (the gold standard) or unattended PSG conducted in patients' homes for the detection of OSA. Unfortunately, there are several barriers to the use of PSG. Within the VHA there are long wait times for scheduling PSG (within or outside of the VHA). Veterans in rural areas often must travel great distances to the nearest sleep laboratory. An alternative to PSG in a sleep laboratory is unattended PSG. Studies have reported good agreement between unattended PSG and formal PSG (sensitivities: 75-100%; specificities: 87-100%). The VHA Sleep-Related Breathing Disorders Source Book states that alternatives to full PSG may be acceptable when patients cannot be assessed with PSG in a sleep laboratory. Other alternative approaches include the use of auto-PAP. Several studies have evaluated the use of auto-PAP devices used diagnostically, finding them to have acceptable validity among stroke/TIA patients.

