### **3. Study Procedures**

#### **5.1 Study Design**

**5.1.a. ASAP Overview** The ASAP project will be conducted as a Hybrid Type I, randomized, stepped-wedge trial at 6 intervention sites and 30 control sites over a 3.5-year period (Figure 1). The 6 intervention sites will begin the 21-month active implementation period; (orange shading for WAVE 1, green shading for WAVE 2 and yellow shading for WAVE 3) in 3 staggered “steps” with 2 sites per step. Immediately following the active implementation phase for WAVES 1 and 2 will be a sustainability phase up to 7 months in duration (purple shading). WAVE 3 will not have a sustainability phase. This design allows for 3 active implementation data periods of 7-months duration for each WAVE. As seen in Figure 1, there are a variable number of 7-month data periods in the baseline and the sustainability periods by wave. The ASAP quality improvement intervention includes a systems redesign Virtual Collaborative and data monitoring. As part of the quality improvement intervention, sites will locally tailor and implement an ASAP approach, in which each site chooses a diagnostic strategy from a menu that includes unattended PSG, in-laboratory PSG, or direct to auto-PAP approach. Similarly, sites may choose any treatment strategy.

Figure 1. ASAP Project Active Implementation and Sustainability Timeline

[figure not shown]

**5.1.b. Participating Sites** To be eligible for inclusion in ASAP a site had to have >50 stroke/TIA patients per year and have at least 1.0 FTE staff dedicated to systems redesign. The sites were chosen because they are diverse in terms of geography and sleep infrastructure. Data regarding the capacity to perform acute OSA assessment at each site is included in site investigators' letters of support. Furthermore, the sleep clinical champions vary across the sites and include clinicians trained in pulmonary, neurology, and psychiatry; some have on-site sleep laboratories whereas others use unattended PSG or fee-basis for their PSGs.

Table 2 data provide the estimates that were used in the revised power calculations: 111 patients per year will be eligible.

| VAMC (Site)       | Annual Patient Volume (n) a | History of OSA (n) | PSG in prior 5-years (n) | Potentially Eligible (n) b |
|-------------------|----------------------------------------|--------------------|--------------------------|---------------------------------------|

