| A                 | 212                                    | 30                 | 18                       | 172                                   |
| B                 | 150                                    | 26                 | 17                       | 111                                   |
| C                 | 169                                    | 52                 | 20                       | 107                                   |
| D                 | 157                                    | 30                 | 23                       | 116                                   |
| E                 | 141                                    | 37                 | 37                       | 92                                    |
| F                 | 172                                    | 39                 | 32                       | 117                                   |
| National average  | 158.2                                  | 37.3               | 25.4                     | 107.5                                 |
| ASAP sites | 157.3                           | 35.2        | 20.3              | 119.2                          |

aAnnual stroke/TIA volume based on FY2017 data and excludes patients with a history of OSA. bPotentially eligible patients exclude those with: history of OSA, PSG in prior 5 years, death within 7-days of discharge, and hospice referral.

**5.1.c. Intervention Description** The quality improvement intervention will include: a systems redesign Virtual Collaborative and data monitoring.

**Systems Redesign Virtual Collaborative** A Virtual Collaborative will be convened among the investigators and the clinical team members from the active implementation sites. The site clinical teams will include members from the stroke team, sleep medicine, and systems redesign. The Virtual Collaborative will be used to develop system redesign approaches to overcome barriers to

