## **5.2 Recruitment Methods**

**5.2.a General Recruitment Overview** As the quality improvement intervention is applied at the facility-level, rather than at the patient-level, the primary unit of analysis for ASAP is at the facility-level. Therefore, given that all six sites have already agreed to participate, recruitment has been completed. The primary effectiveness outcome, evaluated at the facility-level, will be the proportion of patients at each site which undergo and complete diagnostic testing (30-day sleep apnea diagnostic rate) For this rate, the denominator includes all eligible patients at the participating facilities. Because the ASAP program focuses on providers and systems of care, patients will not be consented. Each local site R&D board will be requested to provide approval for research to take place at that location.

ASAP sites will change the standard practice for all eligible ischemic stroke and TIA patients such that the routine clinical experience will be to receive OSA diagnosis and treatment. In the same way that all ischemic stroke/TIA patients receive other guideline-recommended care, patients at ASAP sites will also routinely receive OSA diagnosis and treatment. Certainly, our goal is to encourage all eligible patients to accept the recommendation to receive OSA diagnosis and treatment and the degree of patient acceptance will be a key component of the implementation evaluation, however the concept of recruitment as would be applied in a patient-level clinical trial is not applicable to this facility-level stepped-wedge trial. Similarly, although a patient-level trial would include a detailed description related to participant selection, for this facility-level analysis, patient selection is considered in terms of the patients who will be included in the denominator for each of the effectiveness outcomes as described above. However, the treating provider will determine if any given patient has a contraindication to PAP.

For Health Care Providers, we will request a waiver of documented consent (for interviews). We will record a verbal acknowledgement that the interviews are being recorded. No Health Insurance Portability and Accountability Act (HIPAA) information is being requested or accessed.

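### The primary outcome is defined as PSG completion, but the protocol lets sites diagnose by direct auto-PAP and elsewhere words the outcome as any diagnostic testing

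*Protocol*

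**What the plan says.** All references are to the protocol.

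- **Narrow definition.** Section 5.7.c, Specific Aim 1 analyses: "The diagnostic rate is defined as PSG completion within 30 days of presentation for the index stroke or TIA". The Aim 1 hypothesis in section 2 agrees: "mean facility diagnostic rate (PSG within 30 days of presentation) will be 70% for eligible patients during intervention periods vs 7% for controls".
- **Permitted strategies.** Section 5.1.a: "each site chooses a diagnostic strategy from a menu that includes unattended PSG, in-laboratory PSG, or direct to auto-PAP approach". Aim 1 gives the same three choices, pairs the home sleep test with unattended PSG, and lists auto-PAP separately.
- **Status of auto-PAP.** Section 1 says that "only PSG or auto-PAP (used diagnostically) can identify disease status post-cerebrovascular event", so the protocol treats auto-PAP as diagnostic and as something other than PSG.
- **Broad wording.** Section 5.2.a describes the primary outcome as "the proportion of patients at each site which undergo and complete diagnostic testing". The Diagnostic Rate Analysis paragraph in section 5.7.c specifies a patient-level yes/no outcome of diagnostic testing, without naming PSG.
- **Control sites.** The Control Sites text gives, as its example, comparing polysomnography use in administrative data between intervention sites and matched controls.

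Nowhere does the protocol say that auto-PAP used diagnostically counts as PSG, or that it counts towards the diagnostic rate.

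**The concern.** The numerator of the only primary outcome has two readings, and the one written as a definition leaves out a strategy the programme offers. A site that picks auto-PAP and applies it to every eligible patient would be scored as diagnosing almost nobody. Four things would follow:

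- The estimated effect of ASAP would depend on which strategies the sites happened to choose, as well as on how well they delivered them.
- Aim 3 would be tilted. It hypothesises that sustainability is greatest at sites relying mainly on home sleep tests, and section 5.7.e takes the sustainability effect from the primary-outcome models. Home sleep tests are grouped with PSG and score; auto-PAP does not. The definition therefore leans towards the hypothesis in any comparison with auto-PAP sites.
- The 30-day treatment rate has newly diagnosed patients as its denominator. If that follows the PSG definition, auto-PAP patients drop out there too.
- Active sites receive monthly feedback on these outcomes (section 5.1.d), so an auto-PAP site could be shown as failing while doing what the programme permits.

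**Working it through.** **1. The plan's own figure.** Table 3 gives power of 0.95, 0.93 and 0.93 for 7% versus 15% at CV 0.3, 0.5 and 0.8. The check used the standard stepped-wedge generalised least squares variance with:

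- a random site intercept, τ = CV × 0.07;
- within-site variance 0.07 × 0.93 / 64 per site-period;
- categorical period, and separate active and sustainability terms;
- two sites per step, with power = Φ(0.08/SE − 1.96).

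With six periods (one, two or three control periods, then three active, then two, one or no sustainability periods) this gives 0.951, 0.935 and 0.925. All twelve active-versus-control cells agree within 0.01. Sections 5.7.b and 5.7.c state eight periods; with eight the same formula gives 0.95 to 0.96. That difference is a separate matter. The power figure takes the two rates as given and says nothing about how a patient is scored.

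**2. Scoring at one site.** Let f be the share of tested patients who have auto-PAP and no PSG within 30 days. The protocol gives no value for f, so it is an assumption shown over its range. The true testing rate is the hypothesised 70% and the control rate is 7%.

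Scored rate = 0.70 × (1 − f)

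| f | Scored rate | Difference from 7% |
|---|---|---|
| 0 | 70% | 63 points |
| 25% | 52.5% | 45.5 points |
| 50% | 35% | 28 points |
| 75% | 17.5% | 10.5 points |
| 90% | 7% | 0 |
| 100% | 0% | −7 points |

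The scored rate reaches the 15% used for power at f = 1 − 0.15/0.70 = 79%, and the control rate at f = 1 − 0.07/0.70 = 90%.

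**3. Mean over six sites.** Suppose k sites use auto-PAP only, volumes are equal and the true rate is 70% everywhere.

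- No PSG at those sites: 0.70 × (6 − k)/6
- 7% PSG retained at those sites: [0.70 × (6 − k) + 0.07 × k]/6

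| k | No PSG | 7% PSG retained |
|---|---|---|
| 1 | 58.3% | 59.5% |
| 2 | 46.7% | 49.0% |
| 3 | 35.0% | 38.5% |
| 4 | 23.3% | 28.0% |

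If auto-PAP used diagnostically were counted, the mean would stay at 70% for every k.

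**The case against.** **The broad wording may be the operative one.** The paragraph that specifies the primary model speaks of diagnostic testing, and detailed code lists often sit in an analysis plan that is not shown here. A reader might infer from section 5.7.c that auto-PAP patients will certainly be scored as undiagnosed; the protocol does not support that as fact. What stands is the conflict. Both places that attach a criterion to the rate say PSG, so an analysis plan that counted auto-PAP would contradict them, and one that did not would leave out a permitted strategy.

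**No site is shown to use auto-PAP.** Section 5.1.b mentions on-site laboratories, unattended PSG and fee-basis PSG, all of which are PSG routes. A site may also mix methods, and an auto-PAP patient who completes PSG within 30 days is counted. This stands, and it is why the rates above are scenarios only.

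**PSG-only is a defensible uniform endpoint.** In-laboratory PSG is the reference method, and it is easier to find in administrative data at about 30 control sites. That is a fair argument for keeping it as a sensitivity analysis. It does not explain why the primary outcome should fail to register one of three strategies on offer.

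**The bias runs towards the null.** Provided diagnostic auto-PAP is commoner under ASAP than in usual care, misclassification shrinks the effect and cannot by itself create one. This also stands.

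**Conclusion.** Wrong as written. The explicit definition of the sole primary outcome conflicts with the permitted strategies and with the broader wording of the same outcome. Followed literally, it attenuates the effect at any site using auto-PAP and makes the site and Aim 3 comparisons depend on the strategy chosen. The size is unknown. The illustrative six-site means of 58–60%, 47–49% and 35–39% for one, two or three auto-PAP-only sites assume a true 70% rate, equal volumes, and between 0% and 7% PSG at those sites.

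Three stronger readings are tempting and are not supported:

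- **That the error falls only in intervention periods.** The PSG criterion applies to all sites and periods, and nothing says usual care never uses auto-PAP diagnostically. Mainly during active implementation is as far as the text goes.
- **That the trial is underpowered.** The 7% versus 15% calculation stands on its own terms. A site's 70% falls to 15% only when about 79% of tested patients have auto-PAP without PSG.
- **That the 70% can be re-expressed on a wider denominator.** Table 2 footnote b removes more patients than section 5.4 does. Any converted rate, however, would require that none of the added patients is tested and would turn on how footnote a is read. In every row of Table 2, volume minus eligible lies between the OSA count and OSA plus prior PSG (site A: 212 − 172 = 40, against 30 and 48), so patients with OSA appear to have been subtracted from the volume.

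**What to change.** Reconcile Aim 1 in section 2, section 5.2.a, section 5.7.c (the definition and the Diagnostic Rate Analysis paragraph) and the Control Sites text to one numerator: completion, within 30 days of presentation, of any diagnostic strategy the protocol permits. That means in-laboratory PSG, unattended PSG or home sleep test, or auto-PAP used diagnostically. Ascertain it in the same way at all sites and in all periods, control sites included. Keep PSG-only as a prespecified sensitivity analysis. State whether the newly diagnosed denominator of the treatment rate follows the same definition.

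In the same revision, state the eligible denominator once. Sections 5.2.a and 5.4 should be aligned with Table 2 footnote b, which reads: "Potentially eligible patients exclude those with: history of OSA, PSG in prior 5 years, death within 7-days of discharge, and hospice referral".

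The cost is protocol wording and one more element in the outcome algorithm. Chart review and the National Prosthetics Patient Database are already listed data sources. There are two real drawbacks. PAP issue alone cannot separate diagnostic from therapeutic use, so chart data must make that distinction, including at control sites. And an auto-PAP patient may count in both the diagnostic and the treatment outcome, which should be acknowledged when the two are reported together.
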